### Participants

The trial will recruit 72 autistic adults who have received a diagnosis of autism from one of the three participating clinical services (24 in each service). Participants will be adults (18+years) and will not have a diagnosis of a co-occurring learning disability. Clinicians will not invite individuals with a diagnosed intellectual disability to take part in the study. Participants will be recruited over a 6-month period from 1 April 2025 until 1 October 2025 or until the service target sample (24) has been recruited. The sample size is in line with guidance recommending a sample size of 70 for a two-arm randomised pilot study.^30^

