### Study procedures

Service users who receive a diagnosis of autism and meet the other eligibility criteria (18+ years old, no diagnosis of intellectual disability) will be given information about the study (written information leaflet, verbal information) by their diagnosing clinician which includes links to access further information about the study and contact details for the research team at the University of Sheffield. This will be given alongside other standard care information (eg, signposting to resources, information about their service’s post-diagnostic provision) at the appointment where they receive their diagnosis. The full information sheets for the study have been provided in standard and Easy Read/Plain English versions. Participants will have 4 weeks from the date of their diagnosis to decide whether they would like to participate in the study. They will be able to access a form to consent to participate and to provide their contact details via the links provided in the information leaflet.

Participants will be emailed a link to complete a short demographic questionnaire (age, gender, ethnicity, diagnosing service, date of diagnosis). Following this, they will be randomised into either the assessment group (n*=*36) or the treatment as usual group (n*=*36) by the research team at the University of Sheffield. This will be done using a minimisation approach which allows demographic factors to be balanced across groups in ongoing recruitment. This will be done using software developed by researchers at the University of York^36^ and will balance three factors (gender, age, ethnicity) with two levels for each factor (male/female, under/over 40, white/non-white) in each study arm. All participants will continue with the standard care offered by their clinical site during the study. This may include signposting to resources, follow-on appointments and psychoeducational input. It is not possible to blind participants to group allocation. However, clinicians will not be informed about individual participation or group allocation.

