### Data analysis

Descriptive data for all demographic variables will be presented by trial arm to provide an overview of the cohort of participants recruited to the study, to evaluate the group allocation methods and to demonstrate the representativeness of the sample. Means and SD will be reported for the QoL and mental health measures. These will be compared with clinical cut-offs to indicate levels of well-being in the sample.

Eligibility rate, recruitment rate, completion rates and times for the strengths and needs assessment and the outcome measures will be reported descriptively. Sample medians will be used as an estimate of average completion times. CIs will indicate completion time variance.

Participants will be given 2 weeks to complete the strengths and needs assessment and the QoL/mental health measure questionnaire. After 1 week, they will be sent a reminder and offered support if they need it. After 2 weeks, they will be considered ‘lost to contact’ and will be sent a debrief form with links to support organisations. The number of participants ‘lost to contact’ or withdrawn will be recorded as part of the trial evaluation. If participants start but do not complete the strengths and needs assessment, we will record the time they spend on the assessment and the proportion completed. Any data previously given by participants who are ‘lost to contact’ or withdraw will still be analysed unless participants ask us to withdraw their data.

Preliminary effectiveness of the strengths and needs assessment will be assessed using mixed model analyses of covariance. These analyses will determine whether QoL (assessed using EQ-5D-5L and ReQoL-10) and mental health (assessed using PHQ-9 and GAD-7) changes between baseline and 3 months post-intervention are affected by allocation to the assessment/TAU group. The analyses will statistically control for demographic variables and clinical site. Effect size will be reported using partial eta-squared which will inform the sample size calculation for the definitive trial (RCT).

Qualitative data from the interviews and focus groups will be analysed using NVivo.^45^ Questions pertaining to acceptability and feasibility of the trial procedure will be analysed using thematic content analysis.^46^ Experience of post-diagnostic service provision more generally will be analysed using a reflexive thematic analysis approach.^47^

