The development and implementation of a standardised strengths and needs assessment for autistic adults are in line with the priorities of the NHS long-term plan^11^ and the Department of Health and Social Care’s (2021–2026) strategy,^10^ to improve post-diagnostic support and reduce health inequalities for autistic people. This pilot trial represents a first stage in evaluating these trial procedures in preparation for a larger scale RCT. The three sites included in this pilot have different post-diagnostic support pathways, are in different geographic locations and catchment areas and have different numbers of people coming through their services. This increases the generalisability of the results and the usefulness of the trial process evaluation. A larger scale RCT will then be needed to evaluate whether this assessment could offer a standardised approach to evaluating individual support needs in NHS diagnostic centres.

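### Site is left out of the minimisation although it is known before allocation, determines standard care and is adjusted for in the analysis; adding it is a modest, cheap improvement

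*Protocol article*

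**What the plan says.** Under Study procedures, the protocol article states that the minimisation "will balance three factors (gender, age, ethnicity) with two levels for each factor (male/female, under/over 40, white/non-white) in each study arm". The strengths and limitations box names the same three factors, and Reliability and validity speaks only of demographic factors. No stratification by site is described anywhere.

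Four other statements bear on this:

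- Study procedures: before allocation, participants complete a "short demographic questionnaire (age, gender, ethnicity, diagnosing service, date of diagnosis"), so site is known when the arm is assigned.
- Study procedures: "All participants will continue with the standard care offered by their clinical site during the study".
- Discussion: "The three sites included in this pilot have different post-diagnostic support pathways".
- Data analysis: "The analyses will statistically control for demographic variables and clinical site". This sentence concerns the preliminary-effectiveness models.

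The Participants section sets the recruitment target ("The trial will recruit 72 autistic adults who have received a diagnosis of autism from one of the three participating clinical services (24 in each"), and Study procedures sets the arm sizes ("randomised into either the assessment group (n*=*36) or the treatment as usual group (n*=*36").

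**The concern.** Treatment as usual is both the comparator and the background care in the assessment arm, and its content depends on the site. The authors treat site as worth adjusting for, yet nothing in the allocation aims at 12:12 within a site. A chance imbalance would tie arm to local support package to some degree.

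This matters most where results are reported by arm without adjustment. Primary outcome measures lists attrition in each arm and adherence to the outcome measures as feasibility data, and Data analysis reports completion rates descriptively. The article itself flags higher attrition under treatment as usual as a risk. If sites differ in retention, an uneven split shifts the raw arm comparison of attrition for reasons unrelated to allocation.

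The factor levels have a smaller gap. Gender has two levels, male and female, while eligibility (18 or over, autism diagnosis at one of the services, no intellectual disability) does not mention gender. An eligible adult who is neither has no stated level.

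**Working it through.** **Inputs.** From the article: three sites, 24 each, 36 per arm, one shared recruitment window ("over a 6-month period from 1 April 2025 until 1 October 2025 or until the service target sample (24) has been recruited"). The plan's totals agree: 3 × 24 = 72 = 36 + 36. It states no figure for site balance, so there is none to reproduce.

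**Assumptions.** The article does not give the random element of the minimisation, the factor prevalences or the order of arrival. Arrivals are taken as interleaved across sites, because the window is shared.

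**1. Exact calculation with site ignored and totals fixed at 36:36.**

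For one given site, P(split k:(24−k) or worse) = 2 × Σ[x ≥ k] C(36,x)·C(36,24−x) / C(72,24).

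For at least one site, sum C(24,a)·C(24,b)·C(24,c) / C(72,36) over all a + b + c = 36 in which any site reaches k in either arm.

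| Split or worse | One given site | At least one of three |
|---|---|---|
| 15:9 | 21% | 42% |
| 16:8 | 7.9% | 18% |
| 17:7 | 2.3% | 6.1% |
| 18:6 | 0.5% | 1.5% |

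**2. Simulated minimisation.** Two sets of simulations used interleaved arrivals: 4,000 trials with assumed prevalences of 55/30/12%, and 5,000 trials with 50/30/15%. The assignment probability was 1.0 or 0.8. Figures are for at least one site.

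| | Site left out | Site added |
|---|---|---|
| 15:9 or worse | 42–44% | 0–1.7% |
| 16:8 or worse | 19–20% | 0–0.1% (second set only) |
| 17:7 or worse | 6–7% | 0% (second set only) |

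The agreement with step 1 shows that the assumed prevalences hardly matter. Arrival order does: if sites recruited strictly one after another, 15:9 or worse would occur in only 0–3% of trials even with site left out.

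**3. Cost to the site-adjusted effect estimate.** Relative efficiency is Σ(n1·n0/n) over sites, divided by its value at 12:12 everywhere, 3 × (12 × 12/24) = 18.

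- 15:9, 9:15, 12:12: (5.625 + 5.625 + 6)/18 = 17.25/18 = 96%.
- 16:8, 8:16, 12:12: (5.33 + 5.33 + 6)/18 = 16.67/18 = 93%.
- Over random 36:36 allocations: mean 97%, 5th percentile 91%, below 90% in about 2% of trials.

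**4. Exposure of unadjusted by-arm figures.** Let sites 1, 2 and 3 have attrition a1, a2, a3, with no effect of arm. Under splits 16:8, 12:12, 8:16 the expected arm difference is (16a1 + 12a2 + 8a3)/36 − (8a1 + 12a2 + 16a3)/36 = 8(a1 − a3)/36 = 0.22(a1 − a3). Under 15:9, 12:12, 9:15 it is 6(a1 − a3)/36 = 0.17(a1 − a3). So about a fifth of any retention gap between those two sites appears as a difference between arms.

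On a continuous outcome with site means assumed at −0.5, 0 and +0.5 SD, an unadjusted arm difference carries a chance site error with SD about 0.10 SD (95th percentile of its absolute size 0.19 SD). Adjusting for site removes it.

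**The case against.** The strongest reply is that the plan already deals with site where it compares outcomes between arms. The adjustment removes additive site imbalance at the small cost shown above. A reader might infer that it recovers only part of the damage and leaves the effect estimate confounded with local care. The documents and the arithmetic do not support that.

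Three further inferences also fail:

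- **Interviews.** The plan needs two interviewees per arm per site. Even an 18:6 split leaves six people for two places.
- **Feasibility within site.** No by-arm estimate within site is planned; attrition is specified by arm across the study. With about 12 people per cell, such estimates would be imprecise even at 12:12.
- **Age exactly 40.** The age cut is ordinary shorthand in a condensed article and is no finding.

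It can also be said that 15:9 in any one of three sites is a lenient threshold, that this is a pilot, and that the acceptability item and usability scale are about an assessment completed in one arm only. All of that is fair. Choosing minimisation factors is a design preference, and the article claims balance only on demographics, so it contradicts nothing.

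What remains is that the factor list is stated in full, so its omission of site is not an effect of condensing. The by-arm attrition and adherence figures carry no stated site adjustment. The allocation method is itself under test, since the first research question asks whether the randomisation methods are feasible.

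**Conclusion.** The point holds as a modest improvement. Roughly two trials in five would have at least one site at 15:9 or worse, and somewhat under one in five a site at 2:1 or worse; 3:1 or worse is rare, at about 1.5%. Independent coin tosses would give 39% for 16:8 or worse, but that overstates the risk here because the totals are held near 36:36.

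These figures rest on 24 per site being reached, an overall 36:36 split and interleaved recruitment. The site-adjusted effect estimate loses about 3% of efficiency on average. The main exposure is the raw comparison of attrition and adherence between arms, and its size depends on how far retention differs between sites, which the article does not say. A reader might take this as a threat to the pilot's main conclusions; it is not, because the primary acceptability outcomes do not depend on site balance between arms.

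**What to change.** Add diagnosing service, with three levels, as a fourth minimisation factor. It is already collected before allocation, so no new data are needed, and the allocation would then match the analysis model. In the same edit, add a gender level for participants who are neither male nor female.

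The cost is marginally looser balance on age, gender and ethnicity. The article dates recruitment from April 2025 and sends any protocol modification through a formal amendment, so a change after the start would mean an amendment and a switch of algorithm part-way through allocation. In that case, report allocation and attrition by site and arm, and include site as a factor in the definitive trial.

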Both groups will complete online QoL and mental health questionnaires at baseline (T1) and at 3 months follow-up (T2). Only the assessment group will be asked to complete the strengths and needs assessment. A link to complete the strengths and needs assessment will be emailed immediately after baseline measures are completed. Participants will be told that they can email the researcher with any questions about the assessment or to provide support during the completion process. They will also be told that they can do the assessment in as many sittings as they choose to (responses are saved on the platform continually) and that they can complete the assessment over a 2-week period.

Participants will receive voucher payments of £20 for completing their T1 measures and £10 for completing T2 measures. Participants who do not complete measures will receive a reminder email with contacts for the research team at the University of Sheffield and links to support services.

A subsample of 12 participants (four from each service: two from the Assessment group and two from the treatment as usual group) will also be invited to take part in an interview after T2. They will be provided with additional information for these interviews and will be asked to consent to take part. The interviews will be held mainly online, although some will be hosted in the diagnostic services, if participants prefer, and services have capacity to offer this. The interviews will follow a semi-structured schedule which will cover the acceptability and feasibility of the study procedures and the strengths and needs assessment, any barriers or facilitators to trial participation, any adverse effects of participation and their personal experiences of post-diagnostic support. Interviews will last for around 30 min and will be recorded and transcribed verbatim. Participants will receive voucher payments of £20 for taking part in an interview. Participating clinicians and administrators (involved with the set up or running of the study at each site) will be invited to take part in a focus group at each diagnostic service following the 6-month data collection period. Figure 1 shows the movement of participants through the study.

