### Primary outcome measures

The primary study outcomes are the acceptability and usability of the strengths and needs assessment, and the acceptability and feasibility of the trial procedures. Acceptability of the strengths and needs assessment will be measured using a single item from the TFA^30^: ‘How acceptable was the assessment to you?’. This is answered on a 5-point Likert scale from completely unacceptable to completely acceptable. The SUS^29^ will assess the usability of the assessment. This is a 10-item questionnaire answered on a 5-point Likert scale. Responses are summed and scaled to give an overall usability score which can be used to categorise interventions (eg, poor, ok, good, excellent). The SUS has demonstrated reliability and concurrent validity with measures of perceived and objective usability.^37^

Completion times for the strengths and needs assessment and outcome measures will be recorded and reported using sample medians. For those who drop out, time on task until drop-out will be recorded and reported.

The acceptability and feasibility of the trial procedures will be measured by collecting procedural data from the participating sites (eg, the number of participating clinicians, clinician time required to distribute participant invitations, service user eligibility rates). The study team at the University of Sheffield will collect data on recruitment rates and representativeness, adherence rates for the outcome measures and the attrition rate in each arm of the study. Participant interviews and clinician focus groups will also be used to evaluate the acceptability and feasibility of study procedures, barriers and facilitators to study participation, perceived value in the strengths and needs assessment, and any adverse events associated with the study.

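### Minimisation leaves out clinical site, although diagnosing service is known before allocation and is an analysis covariate; adding it is a cheap improvement with a modest gain

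*Protocol article*

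**What the plan says.** The protocol article (Study procedures) assigns participants 1:1, 36 per arm, by a minimisation that "will balance three factors (gender, age, ethnicity) with two levels for each factor". The strengths and limitations box names the same three factors, and Reliability and validity gives balance on demographic factors as a purpose of the method. No section balances or stratifies allocation by service.

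Elsewhere the article treats site as relevant:

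- **Known before allocation.** Participants first complete "a short demographic questionnaire (age, gender, ethnicity, diagnosing service, date of diagnosis") and are randomised after that (Study procedures).
- **Sets the standard care.** Everyone stays on the care their own service offers (Study procedures), and "The three sites included in this pilot have different post-diagnostic support pathways" (Discussion).
- **Fixed recruitment.** Each of the three services is to contribute 24 of the 72 participants (Participants).
- **Analysis covariate.** "The analyses will statistically control for demographic variables and clinical site" (Data analysis).
- **Interview sampling.** Twelve interviewees are taken as "four from each service: two from the Assessment group and two from the treatment as usual group" (Study procedures).
- **Feasibility outcome by arm.** The team will collect "the attrition rate in each arm of the study" (Primary outcome measures). The site adjustment is stated for the quality-of-life and mental health models, not for this outcome.

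**The concern.** The outcome models adjust for demographic variables and site. The demographic variables are balanced at allocation and site is not, although the field is already in hand. In a trial with three services of 24, a chance imbalance at one of them can be sizeable.

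Two things are at stake. First, the site-adjusted comparison at three months is most precise when each service splits evenly, so uneven splits waste some information. Second, attrition and adherence by arm are primary feasibility measures for which no adjustment is stated. If services differ in retention and the arms are unevenly spread over them, part of any difference between arms reflects site. The article names higher attrition under treatment as usual as a specific worry (strengths and limitations box; Discussion), so this is a contrast readers will look at.

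**Working it through.** **Inputs from the article.** Three services of 24 and two arms of 36: 3 × 24 = 72 = 2 × 36, which reproduces the stated total. There are three two-level minimisation factors, without site.

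**Assumptions not in the article.** One minimisation list runs across all three services. Participants from the services arrive in random order. Factor prevalences are 50/40/15%, with 60/25/10% and 50/60/12% also tried. The preferred arm is followed always (deterministic) or with probability 0.8 (biased coin).

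**Step 1: one given service, exact.** With 36:36 overall and allocation unrelated to site, the number x of a service's 24 who enter the assessment arm is hypergeometric:

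P(x) = C(36, x) · C(36, 24 − x) / C(72, 24)

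Summing both tails gives 21.1% for 15:9 or worse, 7.9% for 16:8 or worse and 2.3% for 17:7 or worse.

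**Step 2: at least one of three services.** A multivariate hypergeometric draw gives 42% for 15:9 or worse and 18% for 16:8 or worse. Simulated minimisation (4,000 trials per setting, prevalences 50/40/15%) gives:

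| Scheme | Any service 15:9 or worse | Any service 16:8 or worse | Largest within-service arm difference: median, 95th percentile |
|---|---|---|---|
| Three factors, deterministic | 41.3% | 17.5% | 4, 10 |
| Three factors, 0.8 coin | 42.5% | 18.6% | 4, 10 |
| Site added, deterministic | 0% | 0% | 0, 2 |
| Site added, 0.8 coin | 1.6% | 0.1% | 2, 4 |

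Prevalences of 60/25/10% (three factors, deterministic) give 41.8% and 18.6%. Across all runs, the range without site is about 41-45% and 18-20%; with site it is about 0-2% and 0-0.2%. The 95th percentile of the overall arm difference is 2 with or without site. Adding site loosens balance on the other three factors by about 0.1-0.2 of a participant on average.

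**Step 3: information in the site-adjusted comparison.** For equal outcome variance, the information is proportional to the sum over services of x(24 − x)/24. At 12:12 everywhere this is 3 × 144/24 = 18. Under the hypergeometric model:

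- Var(x) = 24 × 0.5 × 0.5 × (72 − 24)/(72 − 1) = 4.056
- E[x(24 − x)] = 288 − (144 + 4.056) = 139.94
- Expected information = 3 × 139.94/24 = 17.49
- Expected loss = 1 − 17.49/18 = 2.8%, or about 1.4% on the standard error

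**Step 4: an attrition illustration, with assumed rates.** Let attrition be 5%, 15% and 35% at the three services, the same in both arms. Let treatment as usual hold 10, 10 and 16 participants and the assessment arm 14, 14 and 8.

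- Treatment as usual: (10 × 0.05 + 10 × 0.15 + 16 × 0.35)/36 = 7.6/36 = 21.1%
- Assessment: (14 × 0.05 + 14 × 0.15 + 8 × 0.35)/36 = 5.6/36 = 15.6%

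The gap is 2/36 = 5.6 percentage points with no true arm effect. Pooled attrition is 13.2/72 = 18.3%, so the ordinary standard error of the difference is √(2 × 0.183 × 0.817/36) = 9.1 points, and the gap is about 0.6 of a standard error. A split of 16:8 or worse at one named service, in the direction shown, has probability of about 7.9%/2 = 4%.

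**The case against.** The case against is substantial, and much of it stands.

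- **No error or contradiction.** The stated aim is demographic balance, and the scheme serves it. The article never claims balance by site, and handling site by covariate adjustment alone is a legitimate choice. A reader might infer that leaving site out biases allocation or invalidates the comparison. The document does not support that: chance imbalance is not bias, and the outcome models adjust for site.
- **Standard care is shared within a service.** Both arms at a site receive the same background care, so the contrast is the assessment added to that care everywhere. Different pathways make site a plausible predictor of outcome; they do not confound the arms systematically.
- **The attrition illustration is weak evidence.** Its site rates are assumed, the split it needs is unlikely, and the gap amounts to two people. A reader might infer that site imbalance would produce a false attrition signal. At 36 per arm it lies well within sampling noise, and the article describes no test of attrition between arms.
- **The interview quota is not threatened.** At 16:8 the smaller arm still has 8 people for 2 interviews, and about 5 would remain even at the assumed 35% attrition (8 × 0.65 = 5.2).
- **A single list is an inference.** The article does not say whether the software runs once or separately for each service. One trial-wide list is the natural reading; separate runs per service would largely remove the point.
- **The future allocation method is not fixed.** It would go too far to say the pilot fails to test the procedure the definitive trial needs.

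What survives is that the field is collected before allocation, the analysis uses it, no reason is given for leaving it out, and including it costs almost nothing.

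**Conclusion.** The point holds as a cheap improvement to the design, not as an error. Without site in the scheme, at least one service would split 15:9 or worse in about 41-45% of trials and 16:8 or worse in about 18-20%. The consequences are modest: an expected information loss of about 3% in the site-adjusted comparison, and some mixing of site into attrition and adherence by arm.

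The percentages assume 24 per service as planned, one list across services, and factor prevalences and a coin probability that the article does not give; they moved little over the settings tried. The omission itself is certain from the text. The effect on feasibility readings depends on how far services differ in retention, for which the article has no figures.

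**What to change.** Add diagnosing service (three levels) as a fourth minimisation factor under Study procedures, and keep clinical site as a covariate in the outcome models. The cost is one more field in the software, already collected, a short amendment by the route given under Ethics and dissemination, and the slight loosening of balance shown above.

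The near-complete removal of lopsided splits assumes site is used from the first allocation. Recruitment was planned to finish by 1 October 2025 (Trial status). If it is under way, the factor can apply from the next allocation, with a smaller benefit that has not been quantified here.

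If recruitment is complete, report attrition and adherence by arm within each site, keep the site covariate, and include site in the definitive trial's allocation.
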